### Power and sample size estimate

Mean NET production in CAP-associated sepsis patients is suppressed down to 7,500 arbitrary units (AU) versus 13,200 (SD 2,432) AU in age-matched control neutrophils. At day 4, levels remain suppressed at 8,200 AU (SD 5,100) but, by day 7, patient neutrophils have increased baseline NET production almost back to normal (11,500 AU (SD 6,100), *P* = 0.9) versus normal matched controls. If we assume that statin treatment *in vivo* has a similar magnitude of effect as it does *in vitro* on elderly patient neutrophils (+80% NET production), then 18 patients in each arm would be needed to increase NET production by 5,000 AU from day 0 to day 4 with a power of 0.8, *P* = 0.05. For 90% power we would need 23 patients in each arm. To allow for drop outs due to death and so forth, we intend to recruit 30 patients in each arm. Based on our other preliminary data with 23 patients completing each arm, we would have an 80% power to detect significant increases in both chemotactic velocity (effect size +0.5, ±35%) and ROS production (effect size ±57%). For *in vitro* work on healthy elderly patient neutrophils we typically require 6 to 8 patient samples for mechanistic studies so these patient numbers should be adequate for additional mechanistic work.

### Trial conduct

#### Approach to patients and obtaining informed consent

Patients will be identified on the daily consultant ward rounds that take place on the 40-bed clinical decision unit and 80-bed ICU at the QEHB (approximately 60 to 70 daily admissions). Eligible patients may only be included in the trial after obtaining written informed consent.

Where necessary, informed consent may be sought from the patient’s personal legal representative who may be a relative or close friend. If the patient is unable to give informed consent and no personal legal representative is immediately available, a senior doctor (consultant or registrar) who is not connected with the trial may act as professional legal representative.

A copy of the signed informed consent form will be placed in the patients’ medical records and the originals will be retained by the personal legal representative and by the Principal Investigator in the investigator site file.

#### Randomisation and drug/placebo supply

The trial drug (Simvastatin, 80 mg; trade name Accord) and matching placebo will be manufactured by Sharp Clinical Services Ltd (Crickhowell, UK) according to principles of good manufacturing pratice. Matching IMPs will be supplied and packaged according to the randomisation sequence by Sharpe Clinical Services and delivered to the QEHB pharmacy. Patients will be randomised sequentially by allocating them to the next numbered treatment pack held in the QEHB pharmacy.

#### Administration of investigational medicinal product

Subjects will receive either 80 mg simvastatin or placebo once daily for 7 days or until hospital discharge, whichever is shorter. The first dose of study drug will be administered as soon as possible, ideally within 4 hours of randomisation and all subsequent doses given each morning starting on the following calendar day. The drug will be administered by qualified medical or nursing staff. If patients exceed the liver function test, renal or creatinine kinase entry criteria during drug treatment, IMP administration will be withdrawn.

#### Concomitant medications

Patients taking the following medications are not eligible for participation in the study:

Current or recent statin use within 1 month.Taking itraconazole, ketoconazole, HIV protease inhibitors, nefazodone, ciclosporin, amiodarone, verapamil or diltiazem, fibric acid derivatives (except fenofibrate) or danazol.

Severely ill pneumonia patients are usually treated with a combination of intravenous penicillin and a macrolide antibiotic, typically clarithromycin 500 mg twice a day in our trust. If we were to exclude patients who were taking clarithromycin, the trial would therefore only be able to enrol patients with mild disease or those known to be intolerant of macrolides. This would be a significant barrier to recruitment and limit the generalizability of any finding of the study to the general population. We will therefore not exclude patients who are receiving concomitant clarithromycin or erythromycin from this study.

#### Post-randomisation withdrawals and exclusions

Patients may withdraw or be withdrawn (by the personal legal representative or professional legal representative) from the trial at any time without prejudice. Data recorded up to the point of withdrawal will be included in the trial analysis unless consent to use their data has also been withdrawn. If a patient or legal representative withdraws consent during trial treatment, the trial drug will be stopped but permission will be sought to access medical records to collect data related to the trail as per the protocol until the end of the trial.

#### Blinding/unblinding

All personnel involved in the trial, including patients, clinical staff and research/trial staff, will be unaware of the arm of the study to which the patient is allocated during trial participation. Active and placebo treatment packs of the IMP will be identical in packaging, appearance and contents. The protocol allows for emergency unblinding in the event of serious concerns about patient safety. In the unlikely event that unblinding is required the local investigator will discuss this with the chief investigator. All events will be logged.

#### Monitoring and reporting adverse events

All adverse events and serious adverse events, irrespective of the causal relationship with the trial medications, will be reported to the chief investigator within 24 hours of awareness by the investigator. The chief investigator will inform the sponsor and regulatory authorities. As the IMPs used in this study are licensed in the UK, the expected serious adverse reactions (SARs) will be recorded on the case report form.

#### Data collection

Data will be collected on individual case report forms, designed and utilised by the research team to record patient data until hospital discharge. Submitted data will be anonymised and data stored securely against unauthorised access and accidental loss. Data collected will include demographic details, as well as physiological and ventilator variables that will act as indicators of disease severity. If the subject remains in hospital at 28 or 90 days, survival at these time points will be recorded by research staff.

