#### Secondary outcomes

Secondary outcomes of this trial include parameters describing neutrophil migratory capacity; ROS production; neutrophil phagocytic capacity; safety and tolerability of simvastatin administration within this patient group; biological markers of neutrophil activation (for example, myeloperoxidase), the inflammatory response (for example, IL6), alveolar epithelial and endothelial injury (for example, von Willebrand factor), and systemic endothelial function biomarkers (for example, albumin:creatinine ratio); pulmonary extracellular matrix (ECM) degradation and turnover of peptide; and, finally, the relationship of baseline and changes in parameters described above to clinical relevant outcomes (survival, development of organ failure, admission onto intensive therapy unit, sequential organ failure assessment score, ventilator-free days and muscle wastage during the inpatient stay). These assessments will be made at baseline, on days 4 and 7, and in convalescent samples.

Neutrophil migratory capacity will be measured using a modified Dunn chamber as described previously
[15, 19]; neutrophil ROS production will be measured using a luminol-based assay and phagocytic capacity measured by flow cytometry. Plasma indices of neutrophil activation, the inflammatory response and alveolar epithelial and endothelial injury will be measured by enzyme-linked immunosorbent assay, and systemic endothelial function biomarkers and pulmonary ECM degradation will be measured in urine collected from an indwelling urinary catheter (for full methods, see Additional file
1). These assessments will be made at baseline, on days 4 and 7, and in convalescent samples (≥6 weeks post-discharge).

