#### Trial organisation/oversight

Trial oversight will be provided by a Trial Steering Committee comprising investigators, clinicians and trialists. An independent data monitoring committee will monitor the safety of participants enrolled in the trial through regular review of adverse event reports. An interim analysis of efficacy is not planned.

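### The case report form closes at hospital discharge, so form-based safety follow-up varies with length of stay and, read literally, conflicts with the convalescent assessment of safety

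*Protocol article*

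**What the plan says.** Five parts of the protocol article bear on this.

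- **Data collection.** Case report forms are "designed and utilised by the research team to record patient data until hospital discharge". The only later time points named there are tied to inpatients: "If the subject remains in hospital at 28 or 90 days, survival at these time points will be recorded by research staff".
- **Secondary outcomes.** The first paragraph lists "safety and tolerability of simvastatin administration within this patient group" and ends by timing the assessments at baseline, days 4 and 7 and in convalescent samples. The second paragraph repeats the schedule and dates the last point: "These assessments will be made at baseline, on days 4 and 7, and in convalescent samples (≥6 weeks post-discharge".
- **Administration of investigational medicinal product.** Study drug is given "once daily for 7 days or until hospital discharge, whichever is shorter".
- **Monitoring and reporting adverse events.** All adverse and serious adverse events, whatever their cause, "will be reported to the chief investigator within 24 hours of awareness by the investigator". No closing date is given for this duty. In addition, "the expected serious adverse reactions (SARs) will be recorded on the case report form".
- **Trial organisation/oversight.** An independent committee "will monitor the safety of participants enrolled in the trial through regular review of adverse event reports".

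The Statistical analysis plan section also names duration of hospital stay as a time-to-event outcome, to be reported with hazard ratios.

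**The concern.** Safety is a stated secondary outcome, and the form that holds at least part of the safety data closes on a date that differs between patients. That date is discharge, which happens after randomisation and which the treatment might change. Dosing can stop on the same day, so a patient who goes home early may contribute no form-based observation after the last dose, while a patient who stays for weeks contributes a good deal.

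Two things are at stake. One is consistency: the form closes before the convalescent point at which safety, as written, is still being assessed. The other is comparability: if the arms differ in length of stay, they differ in the time during which an adverse event is likely to be seen and recorded. A difference in recorded events could then arise, or be hidden, with no difference in true rates.

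**Working it through.** The article gives no figure on adverse-event follow-up, so there is none to reproduce; its sample-size figures do not bear on this point. The check is date arithmetic on the stated rules.

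**Inputs**
- L = day of discharge, counted from the first dose. The article gives no length of stay, so a range is assumed.
- Last dosing day = min(7, L), from the Administration section.
- Form closes on day L, from the Data collection section.
- Convalescent sample on day L + 42 or later (6 weeks × 7 days), from the Secondary outcomes section.

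**Formulas**
- Days on the form after the last dosing day = L − min(7, L).
- Largest share of the time to the convalescent sample covered by the form = L / (L + 42).

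| Discharge day L | Last dosing day | Form days after last dosing day | Share of time to convalescent sample |
|---|---|---|---|
| 2 | 2 | 0 | 2/44 = 5% |
| 3 | 3 | 0 | 3/45 = 7% |
| 5 | 5 | 0 | 5/47 = 11% |
| 7 | 7 | 0 | 7/49 = 14% |
| 10 | 7 | 3 | 10/52 = 19% |
| 14 | 7 | 7 | 14/56 = 25% |
| 21 | 7 | 14 | 21/63 = 33% |
| 28 | 7 | 21 | 28/70 = 40% |

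For every discharge up to day 7 the form covers no time after the last dosing day. Beyond that it gains one day for each further day in hospital. In all cases at least 42 days separate closure of the form from the convalescent sample.

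**From coverage to bias.** Suppose events occur at a constant rate over a period of W days, that all events in hospital are recorded, and that a fraction p of events after discharge reaches the investigator. Expected recorded events per patient are then proportional to L + p(W − L). If p = 1, this equals W for everyone and stay does not matter. If p is below 1, the arm with the longer stay records more at the same true rate. The direction therefore follows whichever arm stays longer, and the size depends on L in each arm, on p and on how event rates change over time. The article gives none of these.

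**The case against.** The strongest case on the other side has four parts.

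**Late events have a reporting route.** A reader might infer that reactions after discharge are lost, or that the adverse-event window is the hospital stay. The document does not support that. Reporting is triggered by the investigator's awareness, covers all events and has no cut-off at discharge. An event that becomes known later, including at the convalescent contact, is reportable, and the monitoring committee reviews such reports. This stands. What remains is that awareness is close to continuous on the ward and incidental afterwards, so a passive route still makes detection depend on stay, and the committee sees only what has been reported.

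**The convalescent timing may be meant for laboratory measures.** Both timing sentences speak of samples, and the one that gives 6 weeks closes a paragraph on assays. The first paragraph also lists survival and ventilator-free days, which no sample can measure. The clash with the form's closing date may thus be loose wording. That is fair, and it is why the conflict is put here as a literal reading. If safety was not meant, the article describes no post-discharge safety assessment at all, so clarification is needed either way.

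**An article may leave detail to the full protocol.** The adverse-event period is such a detail, and its absence alone would be no finding. But the article does state when the form closes and does place expected serious adverse reactions on it. The point rests on those statements.

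**Any percentage is assumed.** It is tempting to put a figure on the bias. With assumed mean stays of 8 and 10 days, a constant rate and p = 0, recorded events are in the ratio 8/10 = 0.80, or 20% fewer; with 7 and 10 days it is 30% fewer. These figures only restate the chosen stays. With p = 1 the ratio is 1. Counting patients with at least one event at an assumed 0.1 events per day gives 1 − exp(−0.8) = 55% against 1 − exp(−1.0) = 63%, about 13% fewer. A constant rate is itself doubtful, since events may cluster in the acute illness and during dosing. No such figure should be attributed to this trial.

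**Conclusion.** The point holds as a matter of inconsistency and unequal observation. The form closes at discharge, expected serious adverse reactions are recorded on it, and safety as written is assessed at least 6 weeks later. Form coverage after the last dosing day is 0 days for discharge by day 7 and rises to 21 days for discharge on day 28. These coverage figures follow from the stated rules and need only the assumed range of discharge days.

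The consequence is conditional. The comparison of adverse events between arms could be biased, in either direction, if length of stay differs between arms and events after discharge are less often detected than events in hospital. The document gives no basis for stating that the bias exists or how large it is. The primary outcome, a laboratory measure at 72 to 96 hours, is not affected. The matter should be put right because safety is a named outcome and the remedy is small.

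**What to change.** 1. Reconcile the Secondary outcomes, Monitoring and reporting adverse events, and Data collection sections: say whether safety is assessed at the convalescent point, and when the case report form closes.
2. Keep the form open to the convalescent contact and ask there, with dates, about adverse events and readmissions since discharge. For patients who do not attend, use a record check.
3. State one adverse-event period, fixed from randomisation and the same for every patient whatever the discharge date, and compare the arms over that period. As the convalescent contact falls at least 42 days after discharge, it falls at least 42 days after randomisation for anyone discharged alive. Any period up to 42 days can therefore be completed at that contact. Day 28, already a time point in the Data collection section, is one candidate.

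The cost is a few added questions at a planned contact, or a record check, in at most 60 patients, plus a minor amendment to the text and the form. Awareness-based reporting continues as written, and treatment is unchanged.

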#### Statistical analysis plan

Data will be analysed with the help of a trial statistician. Data will be analysed using SPSS for windows 17.0 (IBM, NY, USA). A detailed analysis plan will be developed during the trial prior to commencement of analysis. In brief, for continuously distributed data, differences between groups will be tested using independent samples *t*-tests with transformations of variables to normality if appropriate or non-parametric equivalents. Chi-squared tests (or Fishers Exact tests) will be used for categorical variables. A *P* value of 0.05 will be considered as significant. We will test for significant correlations between changes in the biological markers using standard methods. The treatment effect will be analysed on an intention-to-treat basis. For the further examination of relationships between a binary variable and known explanatory variables, the following tests will be applied as appropriate. Logistic regression will be used to provide the estimated risk ratios for the treatment effect with associated 95% confidence intervals. Time to event outcomes such as duration of ventilation or duration of hospital stay will be analysed by survival methods and reported as hazard ratios and 95% confidence intervals. A single final analysis is planned at the end of the trial.

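### Survival at days 28 and 90 is planned only for patients still in hospital, so deaths after discharge go unrecorded and this secondary outcome is incomplete in a way that depends on length of stay

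*Protocol article*

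**What the plan says.** The protocol article, under Data collection, sets two rules. Case report forms are "designed and utilised by the research team to record patient data until hospital discharge". For later survival it says: "If the subject remains in hospital at 28 or 90 days, survival at these time points will be recorded by research staff".

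Under Secondary outcomes, baseline values and changes in the biological parameters are to be related to "clinical relevant outcomes (survival, development of organ failure, admission onto intensive therapy unit" and further items. No time point is attached to survival. The same section plans "convalescent samples (≥6 weeks post-discharge", which is a contact after discharge.

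Under Statistical analysis plan: "The treatment effect will be analysed on an intention-to-treat basis". The same section says: "Time to event outcomes such as duration of ventilation or duration of hospital stay will be analysed by survival methods". It names no survival comparison at day 28 or day 90.

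Under Post-randomisation withdrawals and exclusions, for those whose consent is withdrawn during treatment, "permission will be sought to access medical records to collect data related to the trail as per the protocol until the end of the trial".

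**The concern.** The recording rule is conditional on a state that already implies its answer. Someone who is an inpatient on day 28 or 90 is alive, so recording their survival adds no deaths. The patients whose status is uncertain are those discharged alive beforehand, and the article makes no provision for them. Early discharge is expected: under Administration of investigational medicinal product, treatment lasts seven days or ends at discharge if that comes sooner.

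Discharge happens after randomisation, and treatment may affect it. If vital status is followed only as long as a patient stays in hospital, the chance of seeing a death depends on length of stay, and so possibly on arm. What is at stake is whether a 28- or 90-day survival figure could be reported for all randomised patients, and whether relating neutrophil measures to survival would count late deaths as survivors.

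**Working it through.** **The plan's own figures.** The article states no figure for survival. Its sample size is for NET production: a two-sample t-test with a difference of 5,000 AU, SD 5,100 and two-sided 5% significance (two-sided assumed) gives 17.35 and 22.87 per arm at 80% and 90% power. These round up to the stated 18 and 23. They reproduce, but the point does not depend on them.

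**Step 1: what is known for each type of patient.**

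| Course | Planned record | Status at day 28 / day 90 |
|---|---|---|
| Dies in hospital before the time point | Case report form to death | Known: dead |
| Still in hospital at the time point | Survival recorded under the rule | Known: alive, necessarily |
| Discharged alive earlier, gives convalescent sample | Form to discharge, then sample | Day 28 known: alive. Day 90 known only if the sample is taken on or after day 90 |
| Discharged alive earlier, gives no convalescent sample | Form to discharge | Unknown; death and non-attendance are not told apart |

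**Step 2: what the convalescent sample proves.** Let *d* be the day of discharge, counted from randomisation. The sample is taken no earlier than day *d* + 42. Since *d* is at least 0, that is day 42 or later, so every attender was alive on day 28. For day 90, *d* plus the delay must reach 90. With the shortest delay, *d* must be at least 90 − 42 = 48. A patient discharged on day 7 would need a delay of 90 − 7 = 83 days.

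**Step 3: size.** The article gives no discharge rate and no death rate after discharge, so both are assumed here. Let *p* be the share of the 60 patients discharged alive before the time point, and *q* the share of those who then die before it.

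- Patients without a planned status record = 60 × *p*
- Deaths missed = 60 × *p* × *q*

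| *p* | Without record | *q* = 2% | 5% | 10% | 15% |
|---|---|---|---|---|---|
| 60% | 36 | 0.72 | 1.80 | 3.60 | 5.40 |
| 75% | 45 | 0.90 | 2.25 | 4.50 | 6.75 |
| 90% | 54 | 1.08 | 2.70 | 5.40 | 8.10 |

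The range is 36 to 54 patients without a planned record and about 0.7 to 8 missed deaths out of 60. Convalescent attendance would reduce the first number for day 28. It would not reveal any of the missed deaths.

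**The case against.** The strongest reply is that survival may simply mean survival in hospital. The list of clinical outcomes closes with a qualifier about the inpatient stay, which may cover the whole list or only its last item. On that reading the forms capture what is needed. This stands as a possible reading, but the 28/90-day sentence then adds nothing, and the two sections still need reconciling.

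Second, the article is condensed and the sentence does not contain the word *only*; the full protocol may follow everyone. That is possible. But the article does not merely omit follow-up: it states a condition for recording survival and an end to data collection at discharge.

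Third, other routes might reveal late deaths. Serious adverse events go to the chief investigator within 24 hours of the investigator becoming aware of them, with no stated cut-off at discharge. That can bring in some deaths, but it does not create awareness of deaths at home. Record access to the end of the trial is mentioned for withdrawn consent during treatment, not for patients discharged in the ordinary way.

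Fourth, no between-arm test of 28- or 90-day survival is named; survival is listed as something to relate to the biological measures. That is correct, and it limits the severity.

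**Conclusion.** The point holds, at moderate severity and for a secondary outcome only. As written, vital status at days 28 and 90 is planned for patients who must be alive. Deaths after discharge are not planned to be captured, and any 28- or 90-day survival figure would be incomplete in a way linked to length of stay. The size, 36–54 patients without a planned record and about 0.7–8 missed deaths in 60, rests entirely on the assumed discharge and death rates, which the documents cannot narrow.

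Three stronger conclusions that a reader might draw are not supported:

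- *That survival is unknown for everyone discharged early.* Those who give the convalescent sample are known to have been alive on day 28.
- *That every survival comparison is compromised, or that intention to treat fails for survival.* The forms run to discharge for every randomised patient, so in-hospital death can be compared by intention to treat, although its observation window still ends at discharge.
- *That mortality would be grossly inflated.* With, say, 6 in-hospital deaths, 21 discharged and 3 inpatients among 30, deaths over known status would be 6/(6 + 3) = 67%, against 6/30 = 20% dying in hospital. The article proposes no analysis that discards patients known to be alive at discharge. The realistic error is deaths missed after discharge.

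NET production at 72 to 96 hours and the sample size are unaffected.

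**What to change.** Replace the conditional sentence under Data collection with one such as: *Vital status at days 28 and 90 after randomisation, with date of death where applicable, will be recorded for all randomised patients; for those discharged, from hospital or primary-care records, by telephone, or at the convalescent visit.* Give the case report form a place for these entries, and analyse survival in all randomised patients by arm.

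If that follow-up is not wanted, define the outcome under Secondary outcomes as in-hospital survival and drop the 28/90-day wording.

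The first option costs about one records check or call per discharged patient per time point. At the assumed shares that is up to 36 × 2 = 72 to 54 × 2 = 108 checks, and fewer if one check after day 90 that returns the date of death serves both time points. It needs a minor amendment and no extra clinical procedure. The second option costs only a wording change, but gives up survival over a fixed period.
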